### Cost analysis

The following cost categories will be distinguished and included in this study: intervention costs, costs for the health care sector, patient and family costs and costs outside the health care sector. Intervention costs will include all the costs that contribute to the development and administration of the SMI and Augmented CBT. Health care sector costs are related, for instance, to general practitioner (GP) visits, hospital visits and medication. Patient and family costs concern, for instance, travel costs, costs of informal care, productivity losses and home adjustments. Costs outside the health care sector will be measured as productivity costs.

To measure the actual use of resources, data will be obtained using combined sources (registrations by professionals and a cost questionnaire for the patients conducted at al measurement points, T0 - T3, of both the Self-Management study and the Augmented CBT study). Resources used relating to the interventions will be based on the registered time all professionals spent on the treatment. All use of resources by the patient and their family, within and outside the health care sector will be measured by means of a cost questionnaire which will continuously record volumes of utilization during the follow-up period. The cost questionnaire has been designed especially for the participants in both RCTs, based on existing questionnaires [30]. The questionnaire consists of 20 items and will cover three areas of expenses, namely expenses of (inability to perform) daily activities, expenses of health care consumption and expenses of help received (material and immaterial).

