### €-Restore4Stroke outcome measures

All studies included in the €-Restore4Stroke project will be performed from a societal perspective meaning that all costs and outcomes of both the interventions and comparators will be included. Within the Restore4Stroke programme, Quality of life (QOL) is considered both from a general Health-Related Quality Of Life (HRQOL) and domain-specific QOL perspective. The general HRQOL perspective is operationalised as disease-specific HRQOL measured with the Stroke Specific Quality of Life (SS-QoL [15]), and generic HRQOL measured with the 5-dimensional EuroQol (EQ-5D [16]). The domain-specific perspective consists of the domains: participation measured with the Utrecht Scale for Evaluation and Revalidation Participation (*Utrechtse Schaal voor Evaluatie en revalidatie - Participatie *or USER-p [17]), emotional functioning measured with the Hospital Anxiety and Depression Scale (HADS [18]) and subjective well-being measured with 3 satisfaction questions. An overview of the primary and secondary outcome measures of all studies embedded in the Restore4Stroke programme is presented in Table 1.

**Table 1 T1:** Outcome measures Restore4Stroke (x: cost questionnaires, p: primary outcome measure, s: secondary outcome measure)

	Self-Management study				Augmented CBT study				Cohort study				
	T0	T1	T2	T3	T0	T1	T2	T3	T1	T2	T3	T4	T5

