### Valuation

The valuation of health care costs, patient and family costs will be based on the updated Dutch manual for cost analysis in health care research [31]. This manual recommends using standardised cost prices. In brief, the manual recommends that prices of informal care should be based on shadow prices for unpaid work (meaning a standard cost price based on general hourly wages). Costs of transport will be calculated as the mean distance per destination multiplied by costs per kilometre. Costs of medication will be calculated using prices based on the Daily Defined Dosage (DDD) taken from the Dutch Pharmacotherapeutic Compass [32], indicating the mean medication usage per adult a day, including the government-imposed discount for patients paid by the pharmacy. Productivity costs will be calculated by means of the friction cost method based on a mean added value of the Dutch working population. The friction costs method takes into account production losses confined to the period needed when it is necessary to replace a sick employee (currently 160 days [31]). In case of uncertainty we will use a conservative estimate (i.e. the lowest cost price). Cost prices will be expressed in Euros on the basis of cost prices of 2011. If necessary, existing cost prices will be updated to 2011 using the consumer price index (CPI) [32]. In this case, discounting is irrelevant as the follow-up period is less than a year.

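### The costing rules overlap on productivity, define intervention costs without the comparators but with one-off development, and treat the lowest price as conservative; each can bias incremental cost

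*Protocol article*

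**What the plan says.** The Cost analysis section for the two trial-based evaluations names four categories to be distinguished and included: "intervention costs, costs for the health care sector, patient and family costs and costs outside the health care sector". It then describes them.

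- **Patient and family:** "Patient and family costs concern, for instance, travel costs, costs of informal care, productivity losses and home adjustments".
- **Outside the health care sector:** "Costs outside the health care sector will be measured as productivity costs".
- **Intervention:** "Intervention costs will include all the costs that contribute to the development and administration of the SMI and Augmented CBT". Resource use is measured as follows: "Resources used relating to the interventions will be based on the registered time all professionals spent on the treatment".

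The €-Restore4Stroke outcome measures section says of the societal perspective that "all costs and outcomes of both the interventions and comparators will be included".

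The Valuation section gives one method for productivity ("Productivity costs will be calculated by means of the friction cost method based on a mean added value of the Dutch working population"). It relies in general on the standard prices of the Dutch costing manual, and it adds: "In case of uncertainty we will use a conservative estimate (i.e. the lowest cost price").

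The Statistical analysis section forms the ICER from total cost in each arm, Ci and Cc, and plans a multi-way sensitivity analysis in which prices and volumes may run from minimum to maximum. The Valuation section of the cost-of-illness (COI) study says that its valuation will be similar.

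**The concern.** Ci − Cc is the numerator of every ICER in both trials, so the rules that build the two totals need to be unambiguous and symmetric between arms. Three rules are not.

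1. The categories are not mutually exclusive. An analyst who fills each category as described and adds them up would enter productivity twice.
2. The definition of intervention costs names only the new treatments, which conflicts with the general statement that comparator costs are included. It also brings in development. Development is spent once, so its cost per patient depends on how many patients share it and not on what it costs to treat one more.
3. A low price is conservative only if a lower cost works against the claim being made. In a comparison of two arms it does so only when the new arm uses less of the item.

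**Working it through.** The article gives no cost figures, so there is no stated result to reproduce. The check is algebra on Ci − Cc, plus staff hours from the Interventions section.

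**Productivity entered twice.** Let dO be the between-arm difference in all other costs and dP the difference in productivity cost.

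- Correct increment: dO + dP. Counted twice: dO + 2dP. Error: dP.
- Illustration with dO = €1,000: for dP = −€300 the increment is 400 instead of 700; for dP = 0 it is 1,000 either way; for dP = +€300 it is 1,600 instead of 1,300.

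The error can go either way and vanishes if the arms do not differ on productivity. Each arm's own total would still be too high by its productivity cost.

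**Comparator delivery left out, Self-Management study.** Inputs: two therapists, six sessions of 2 h and one booster; for education, one professional, three sessions of 1 h and one booster. Booster lengths are not given; I assume 1–2 h.

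- SMI: 2 × (6 × 2 + 1 to 2) = 26–28 staff hours per group.
- Education: 1 × (3 × 1 + 1 to 2) = 4–5 staff hours per group.
- Overstatement = education hours ÷ true difference:

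| SMI h | Education h | True difference | Overstatement |
|---|---|---|---|
| 26 | 4 | 22 | 18.2% |
| 26 | 5 | 21 | 23.8% |
| 28 | 4 | 24 | 16.7% |
| 28 | 5 | 23 | 21.7% |

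These are hours per group, not a share of total incremental cost.

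**Comparator delivery left out, Augmented CBT study.** Both arms have 13–16 sessions. If a control session costs a fraction f of a CBT session, omission overstates the delivery increment by f/(1 − f): 11% at f = 0.1, 25% at f = 0.2 and 100% at f = 0.5. The article does not give f. It describes the computer programme as largely self-supporting, which points to the lower values.

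**Development cost.** A one-off sum D spread over the 53 patients per arm in the Sample size calculation adds D/53 to the increment. For an illustrative D of €10,000 to €50,000 this is 10,000/53 ≈ €190 to 50,000/53 ≈ €940 per patient. With only the new arms' development named, the sign is fixed against the new treatment.

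**Lowest price.** Let dV be the between-arm difference in volume. The error in the increment is dV × (p_low − p_true). With illustrative prices of €50 (lowest) and €75 (true):

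- dV = +2: 2 × (50 − 75) = −€50, which favours the new arm.
- dV = 0: no error.
- dV = −2: +€50, which disfavours the new arm.

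The COI study estimates a total V × p, so the error V × (p_low − p_true) is never positive and burden is understated. In the sensitivity analysis, an item whose base-case price is already the minimum can move only upward.

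**The case against.** The strongest reply is that this is loose wording in a condensed article and that a sensible analyst would do the right thing.

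- **Productivity.** The patient-and-family list is only illustrative. Patient and family resource use comes from one questionnaire, and productivity is valued by one method, so there is one amount to enter. The two mentions might even be different losses, such as the family's and the employer's. This stands as far as it goes: the text does not instruct anyone to add the amount twice. But nothing in it separates two kinds of loss, and no rule assigns productivity to one category. The COI questionnaire, by contrast, keeps it in its own subscale.
- **Comparators.** A reader might infer that the comparators will not be costed at all. The documents do not support that. The outcome measures section includes their costs, the registered-time sentence is not limited to the new arms, Cc is a total cost, and the article calls the control programmes interventions too. What remains is a definition that contradicts the general statement. Nor does this reply reach development costs, which are named for the new treatments only.
- **Lowest price.** The rule applies only under uncertainty. A reader might infer that the whole base case sits at minimum prices; it does not, because standard manual prices are the default. The sensitivity analysis would also expose the price choice. For the uncertain items, however, the label is wrong and the range is one-sided.

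A reader might also infer that incremental cost is biased by construction. That goes too far, because the double-count and price errors have no fixed sign and can be zero.

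**Conclusion.** The point holds as a set of rules that should be corrected because each can bias incremental cost if followed as written. There is a risk of double counting productivity. The intervention-cost definition contradicts the stated inclusion of comparator costs and loads one-off development on the new arms. The lowest-price rule is not conservative for a difference between arms and understates burden in the COI study.

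The size cannot be derived from the article. The only figure based on its own numbers is the 17–24% overstatement of incremental staff hours in the Self-Management study. It needs boosters of 1–2 h and a literal application of the definition against the outcome measures section. All euro amounts, the price pair and the fraction f are illustrations.

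**What to change.** 1. Place productivity losses in one category and state that they are counted once.
2. Reconcile the intervention-cost definition with the outcome measures section: state that delivery of both arms is costed by the same registered-time method, including comparator staff time and software.
3. Report the base case without one-off development costs and show them as a scenario.
4. For uncertain items, use the standard or best-estimate price in the base case and the lowest and highest prices in the sensitivity analysis. Apply the same rule in the COI study.

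Items 1, 3 and 4 are wording. Item 2 also needs time registration for comparator sessions by the staff who run them. The Current study status section says that data collection has yet to start, so this can be arranged now; session time that is not registered as it is spent may not be recoverable later.

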### Valuation

The valuation of health care costs, patient and family costs will be based on the updated Dutch manual for cost analysis in health care research [31]. This manual recommends using standardised cost prices. In brief, the manual recommends that prices of informal care should be based on shadow prices for unpaid work (meaning a standard cost price based on general hourly wages). Costs of transport will be calculated as the mean distance per destination multiplied by costs per kilometre. Costs of medication will be calculated using prices based on the Daily Defined Dosage (DDD) taken from the Dutch Pharmacotherapeutic Compass [32], indicating the mean medication usage per adult a day, including the government-imposed discount for patients paid by the pharmacy. Productivity costs will be calculated by means of the friction cost method based on a mean added value of the Dutch working population. The friction costs method takes into account production losses confined to the period needed when it is necessary to replace a sick employee (currently 160 days [31]). In case of uncertainty we will use a conservative estimate (i.e. the lowest cost price). Cost prices will be expressed in Euros on the basis of cost prices of 2011. If necessary, existing cost prices will be updated to 2011 using the consumer price index (CPI) [32]. In this case, discounting is irrelevant as the follow-up period is less than a year.

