### Timeline

For the Self-Management study, eligible patients and their informal caregivers will be randomized towards the Self-Management Intervention (SMI) or education intervention after baseline measurement T0. Both SMI and education intervention have a duration of 10 weeks and post-treatment measurement (T1) will take place at 3 months after T0. Two follow-up measurements (T2 and T3) will take place at 6 and 12 months after T0. For the Augmented CBT study, eligible patients will be randomized towards the Augmented CBT intervention the computerized cognitive training intervention after baseline measurement T0. Post-treatment measurements (T1) will take place 4 months from T0, and two follow-up measurements (T2 and T3) will take place 10 and 16 months from T0. Cost measurements for both studies are presented in Figure 3. At all measurement points, cost data will be asked retrospective varying from 2 to 6 months retrospective.

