### Timeline

Cost measurements are conducted at 2 months (T2), 6 months (T3), 1 year (T4) and 2 years (T5) post stroke, which is parallel to the measurement points of other questionnaires included in the Cohort study. Retrospective data covering a fixed period prior to measurement points will be extracted from the questionnaires: 2 months at T2, 4 months at T3, 6 months at T4 and 6 months at T5. To avoid recall bias after the two year follow-up, a fixed period of maximum 6 months prior to T5 is chosen. An overview of the timeline for the cost-of-illness cost measurements is presented in Figure 4.

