### Cost analysis

Essentially, there a two approaches to establish the costs of illness: the top-down approach and the bottom-up approach [37]. Scientific publications so far show that the majority of COI studies have been performed using a top-down method, based on calculating the costs of a disease through national databases [8]. The COI study described in this article is designed to use a bottom-up method in which a group of patients who have suffered from a stroke (the cohort population) will be asked what the costs of their disease are, through a specially designed cost questionnaire, instead of using databases. The estimation of costs will be divided into two steps. The first step is estimating the quantity of health inputs used and the second step is to estimate the unit costs of the inputs used [38]. The costs are then estimated by multiplying unit costs by the quantities. One of the main advantages of the bottom-up approach is that detailed data can be obtained regarding costs outside the health care sector such as the productivity losses, which will be investigated in this study [37]. Other advantages are that the bottom-up approach is much more accurate in measuring costs than the top-down approach, which is more likely to present misallocation of costs [38]. For example, national health care expenditures may either under or overestimate the total direct costs, where the bottom-up approach gives a more accurate estimate. Furthermore, a serious problem with the top-down approach is that all costs are attributed to the primary diagnosis [37]. This is a serious problem considering that a relevant part of all hospital discharges involve patients with multiple diagnoses. This is not an issue, and therefore an advantage, with the bottom-up approach. In addition, a follow-up period of 2 years will be used in this study, which will make it possible to distinguish patterns in health care consumption over time.

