### Valuation

Within the COI study, the valuation of health care consumption, productivity losses and the costs of informal health care will be similar to the trial-based economic evaluation. This means that the valuation in general will be based upon the Dutch manual for cost analysis in health care research [39].

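### The plan sets discounting aside because follow-up is under a year, but the Self-Management trial runs 12 months (a wording error only) and the Augmented CBT trial 16 months

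*Protocol article*

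**What the plan says.** The Valuation section shared by the Self-Management and Augmented CBT evaluations ends by saying that "discounting is irrelevant as the follow-up period is less than a year".

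The Timeline section for the same trials gives these schedules:

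- Self-Management: "Two follow-up measurements (T2 and T3) will take place at 6 and 12 months after T0".
- Augmented CBT: "two follow-up measurements (T2 and T3) will take place 10 and 16 months from T0".

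The Cost analysis section has patients complete the cost questionnaire at all measurement points, "T0 - T3, of both the Self-Management study and the Augmented CBT study". Table 1 schedules the EQ-5D at T0 to T3 in both trials. Statistical analysis then defines the ICER with yearly total costs in the numerator and effects at 6 months in the denominator.

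The cost-of-illness (COI) study has its own, longer schedule: "Cost measurements are conducted at 2 months (T2), 6 months (T3), 1 year (T4) and 2 years (T5) post stroke". Its Valuation section says that the valuation of its cost categories "will be similar to the trial-based economic evaluation", and does not mention discounting.

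**The concern.** The article does not leave discounting open for a later document. It takes a position and gives a reason, and the reason is a statement about follow-up length that the Timeline section contradicts for both trials. An analyst who follows the Valuation section as written would apply no discounting to the CBT trial, although a quarter of its follow-up (4 of 16 months) lies beyond the first year.

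At stake are the cost and QALY totals per arm in the CBT evaluation, if they cover the whole follow-up. There is also a question of clarity for the COI study, which borrows its valuation approach from the trials but follows patients for twice the 12 months of the Self-Management study.

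**Working it through.** **Step 1. Test the stated reason.** The article gives no discounting figure to reproduce; the only figure is that follow-up is under 12 months.

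| Evaluation | Last measurement | Under 12 months? | Months beyond 12 | Share of follow-up |
|---|---|---|---|---|
| Self-Management | 12 months | no | 0 | 0% |
| Augmented CBT | 16 months | no | 4 | 4/16 = 25% |

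The reason fails in both trials. It could affect the analysis only in the CBT trial.

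**Step 2. Size in the CBT trial, if all 16 months are analysed.** The article names no discount rate, so r = 1.5% to 5% per year is an assumption. Also assumed: even accrual, year 1 undiscounted, and months 13-16 divided by (1 + r).

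Ratio of discounted to undiscounted total = (12 + 4/(1 + r)) / 16

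| r | Ratio | Reduction on discounting | Overstatement if not discounted (1/ratio - 1) |
|---|---|---|---|
| 1.5% | 15.9409/16 = 0.9963 | 0.37% | 0.37% |
| 3% | 15.8835/16 = 0.9927 | 0.73% | 0.73% |
| 4% | 15.8462/16 = 0.9904 | 0.96% | 0.97% |
| 5% | 15.8095/16 = 0.9881 | 1.19% | 1.20% |

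Arm totals are therefore overstated by about 0.4-1.2%. Continuous discounting from time zero, (1 - (1 + r)^(-t)) / (t ln(1 + r)) with t = 16/12, would give reductions of 0.99-3.18%. That convention also discounts the first year, which the plan's reasoning would leave alone, so the stepped figures are the relevant ones.

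**Step 3. Self-Management.** With year 1 undiscounted, the ratio is 12/12 = 1 and nothing changes.

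**Step 4. From arm totals to the ICER.** The ICER is a ratio of differences.

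- If the cost and QALY differences both accrue evenly and share one rate, the factor cancels: at 5%, 0.9881 × ΔC / (0.9881 × ΔE) = ΔC/ΔE.
- If the whole cost difference falls in year 1 and the QALY difference accrues evenly, discounting raises the cost per QALY by 1/0.9881 - 1 = 1.2% at 5%.

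Patterns between these two give a smaller change than the second. The article has no data on accrual, so this is illustration only.

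**Step 5. The COI study.** Two quantities need to be kept apart.

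- A cumulative 24-month total, if one is reported: (12 + 12/(1 + r)) / 24 gives reductions of 0.74%, 1.46%, 1.92% and 2.38% at 1.5%, 3%, 4% and 5%.
- The comparison of year 1 with year 2, which is the cross-year analysis that the COI Statistical analysis section specifies. It asks whether costs changed. Discounting year 2 would build in an apparent fall of 1 - 1/(1 + r) = 1.48% to 4.76%. Undiscounted costs at constant 2011 prices suit this contrast.

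**The case against.** **The ICER may never use months 13-16.** Statistical analysis defines costs as a yearly total and effects at 6 months. Read literally, nothing after month 12 enters the ratio. This stands as a limit: the effect in the CBT trial is conditional. It does not rescue the sentence, which argues from follow-up length rather than from a shortened analysis period, and a one-year cost total is still not less than a year. Nor do the definitions fit the CBT schedule, whose post-baseline visits fall at 4, 10 and 16 months, with none at 6 or 12. No section excludes the later data.

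**The analysis period may have been meant to be shorter.** Outcome measures computes QALYs from three time points, while Table 1 schedules four. If the first three visits were meant, the QALY period would be 6 months (Self-Management) or 10 months (CBT), both under a year. The article does not say which three, and yearly costs do not match that reading.

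**The effect is small.** This is true. CBT sessions all fall within the first four months, so any difference in intervention cost would be untouched by discounting after month 12. The reason to act is that a stated rule rests on an incorrect fact and is cheap to correct.

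**A reader might infer that the under-a-year rule governs the COI study too, so that its second-year costs are overstated by 1.5-5%.** The documents do not support this. The rule is worded for the case in hand, within the trial section. The COI Valuation section says that "productivity losses and the costs of informal health care will be similar to the trial-based economic evaluation", which is not the same as identical, and it does not mention discounting. Beside "a follow-up period of 2 years will be used in this study", the under-a-year reason could not sensibly be meant to apply. The percentage would also be wrong for the comparison that is specified, which belongs on undiscounted costs. What remains is a useful clarification.

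**Conclusion.** The contradiction is certain: the Valuation section's reason for not discounting is wrong for both trials. In Self-Management it is a wording error with no effect on the analysis.

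In Augmented CBT the effect is conditional on the evaluation using its full 16 months. Arm totals would then be overstated by about 0.4-1.2%, assuming annual rates of 1.5-5%, even accrual and an undiscounted first year. The effect on the ICER is probably smaller and may cancel; it would be unlikely to change a conclusion. The underlying weakness is that the article does not state the analysis horizon of each trial, and the discounting rule depends on it.

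For the COI study the documents do not show that the rule was carried over, so no bias is claimed there. This is a modest point that should be corrected.

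**What to change.** 1. **Valuation (trials).** Replace the sentence on discounting. State that none is needed over the 12-month Self-Management horizon.
2. **Horizon.** State the analysis horizon for costs and for effects in each trial, and reconcile it with the yearly costs and 6-month effects in the ICER definition under Statistical analysis. The CBT trial has no visit at 6 or 12 months.
3. **Augmented CBT.** Either discount costs and QALYs after month 12 at a named rate with its source, with 0% as a sensitivity analysis, or restrict the horizon to 12 months explicitly and say how the 10- and 16-month visits supply it. The article gives no rate, so the sponsor must name one.
4. **Valuation (COI).** Add that the under-a-year statement does not apply to the 2-year follow-up. Discount second-year costs only in a cumulative 24-month total, if one is reported, and leave the year 1 versus year 2 comparison undiscounted.

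The cost is a few sentences, one multiplication in the cost and QALY syntax, and one extra sensitivity run. No new data, visits or patients are needed.
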